### Strategies to improve adherence to interventions {11c}

The POWERbreathe KH2 device is equipped with data logging functionality to record each session’s performance, ensuring objective tracking of adherence. Additionally, both IMT and placebo interventions will be provided to participants at no cost as a motivational incentive.

### Relevant concomitant care permitted or prohibited during the trial {11d}

No specific concomitant treatments are prohibited during the trial, except for concurrent participation in other clinical studies that could interfere with IMT outcomes.

### Provisions for posttrial care {30}

No trial-related harm is anticipated. As such, no compensation or special posttrial care arrangements are applicable.

### Outcomes {12}

Primary and secondary outcomes will be assessed by trained research staff who remain blinded to treatment group allocation throughout the study.

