### Criteria for discontinuing or modifying allocated interventions {11b}

During each training session, therapists will closely monitor vital signs and subjective symptoms. The discontinuation criteria are outlined in item 11a. Any adverse events will be documented in the daily training log. If a participant meets two or more discontinuation criteria on three consecutive training days, they will be withdrawn from the study.

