#### Secondary outcomes

The secondary outcomes include changes in peak inspiratory flow (PIF), airway clearance ability, anxiety levels, quality of life, the decannulation rate, and the incidence of adverse events.

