## Assignment of interventions: blinding

### Who will be blinded {17a}

This is a single-blind trial. The participants will be blinded to group assignment. Owing to the nature of the intervention, it is not feasible to blind the therapists conducting the training. However, outcome assessors and the data analyst will remain blinded to the group allocation to minimize bias during outcome analysis.

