### Adverse event reporting and harms {22}

Although this study is associated with minimal known risks, participants are instructed to immediately notify the responsible physiotherapist of any adverse or serious events. The possible side effects may include fatigue, dizziness, or transient decreases in blood oxygen saturation. Any adverse events will be promptly reported to the Institutional Research Ethics Committee by the designated principal investigator.

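### Blinded assessment is claimed for every secondary outcome, but the adverse-event routes described run through therapists who cannot be blinded

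*Protocol article*

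**What the plan says.** The blinding claim in Outcomes {12} has no exception: "Primary and secondary outcomes will be assessed by trained research staff who remain blinded to treatment group allocation throughout the study". The list under Secondary outcomes ends with "quality of life, the decannulation rate, and the incidence of adverse events", so the claim covers adverse events.

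Three places in the article describe how adverse events come to notice:

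- Item 11b, on monitoring: "During each training session, therapists will closely monitor vital signs and subjective symptoms".
- Item 11b, on recording: "Any adverse events will be documented in the daily training log". The sentence does not name the person who makes the entry.
- Item 22, on reporting by participants: "participants are instructed to immediately notify the responsible physiotherapist of any adverse or serious events".

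Item 17a sets out who is blinded. For participants: "The participants will be blinded to group assignment". For the therapists: "it is not feasible to blind the therapists conducting the training". For the remaining roles: "outcome assessors and the data analyst will remain blinded to the group allocation to minimize bias during outcome analysis".

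Item 20a plans a descriptive summary of adverse events by frequency and severity, without a test.

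**The concern.** The article gives adverse events the protection of blinded assessment in one section. In others it describes a procedure that does not provide it. As worded, a reader of the trial report would take the safety table to be as well protected against observer bias as the primary outcome.

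This matters because safety is one of the questions the trial sets out to answer. It is among the secondary objectives in item 7, the Discussion words it as part of the primary objective, and the abstract expects evidence on it. An observer who knows whether a load is applied may ask more readily about fatigue or dizziness in the loaded arm, may grade the same complaint differently, or may be more or less complete in the log. Any of these could create a difference between the arms or hide one.

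**Working it through.** No figure in the plan depends on this point, so the check is a comparison of sections.

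**1. Does the blinding claim reach adverse events?** Yes. Outcomes {12} covers primary and secondary outcomes without exception, and adverse-event incidence is listed as secondary.

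**2. Who first observes or receives the event?** Within sessions it is the therapist (item 11b). When a participant reports, it is the responsible physiotherapist (item 22). Both are on the unblinded side of item 17a.

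**3. Where is it written down?** In a log that belongs to the training sessions (item 11b). Blinded staff are described as recording elsewhere, directly on the CRF that both of them sign (item 18a).

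**4. Does any other section supply a blinded step for adverse events?**

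| Section | What it provides | Blinded adverse-event ascertainment? |
|---|---|---|
| Item 18a | Two blinded staff at each outcome assessment | Not mentioned |
| Item 21a | Safety monitoring by the coordinating center | No: oversight |
| Item 22 | Reporting to the ethics committee | No: follows detection |
| Item 23 | Biweekly steering committee review of recorded events | No: follows recording |
| Tracheotomy tube extraction rates | Blinded clinicians decide on decannulation | Yes, but for decannulation only |

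The last row is informative. For decannulation the article says who is blinded and at which step. It makes no such provision for adverse events.

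**5. Does the stated limitation cover it?** The Discussion names unblinded physiotherapists as a source of performance bias and offers blinded assessors as partial mitigation. On the routes described, that mitigation does not reach events observed and received by the physiotherapists themselves.

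**6. Which events are exposed?** Item 22 names three possible side effects: fatigue, dizziness and a transient fall in oxygen saturation. The first two are subjective and the third is measured. The pause criteria in item 11a include numeric limits for respiratory rate, SpO₂, blood pressure and heart rate, which leave less room for judgement. The exposure is therefore mainly in subjective complaints, in severity grading (for which no grader is named) and in completeness of recording.

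**7. Scale.** With 35 participants per arm, one participant more or fewer with a recorded event moves that arm's rate by 1/35 = 2.9 percentage points. This shows how sensitive the table is to a single entry. It is not an estimate of bias.

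**The case against.** The strongest reply is that logging an event and assessing it as an outcome are separate steps. Item 11b is in the passive voice and names no recorder. Item 22 is a safety-notification instruction rather than an outcome procedure. The blinded staff in item 18a are tied by cross-reference to the Outcomes section, which includes adverse events, and nothing forbids them to ask. This stands in part: it is an inference from silence that therapists are the only route, and blinded review is not excluded. It does not rescue the claim, because the article describes no such review, and events that are not noticed or logged cannot be reviewed later.

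Other points stand and limit the concern. Participants are blinded, which should reduce differential self-report, although their reports go to an unblinded person. Item 11b applies to each session without distinguishing the arms, and controls follow the same evaluation protocol. Therapists must watch for harm in any case. No formal test is affected.

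Two stronger readings are tempting, and the document does not support either.

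- A reader might infer that participants go unobserved on non-training days, since a 14-day window with 10 sessions leaves 14 − 10 = 4 days. The abstract says that adverse events are recorded systematically throughout the study. Eligibility requires suctioning at least 10 times a day, and item 11a provides rehabilitation nursing, so staff contact can be expected every day. The count of four is not fixed either: two Monday-to-Friday weeks span 12 days from first to last session and leave 12 − 10 = 2.
- A reader might want to express differential logging as a ratio between the arms. The document gives no event rate and no capture probability, so any such ratio would be invented.

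Agitation should also not be counted among the expected side effects. It is a pause criterion in item 11a and is not on the list in item 22.

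**Conclusion.** The concern holds in a limited form. The article claims blinded assessment for all secondary outcomes, and the adverse-event procedure it describes does not deliver it. This is a contradiction between statements in the text, so it is not answered by saying that a journal article leaves detail to the full protocol.

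The size and direction of any bias are unknown. The primary outcome, the sample size and the planned tests are unaffected. What is at stake is the credibility of a descriptive safety comparison that the trial presents as one of its aims.

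The conclusion assumes that the routes described are the ones that will be used. If the full protocol gives the blinded assessors an adverse-event task, the remedy reduces to saying so in Outcomes {12} and item 22.

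**What to change.** 1. Amend the sentence in Outcomes {12} so that adverse events logged by therapists are exempt from the blinding claim.
2. Extend the limitation in the Discussion from performance bias to the ascertainment of adverse events by unblinded therapists.
3. Have the two blinded assessors in item 18a put one short, fixed adverse-event checklist to every participant in both arms at the existing outcome assessments. The questions should not refer to the training load, so that the answers do not reveal the arm.
4. Grade the severity of all events, from the log and from the checklist, from a listing without arm labels. Report the two sources separately by arm.

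In-session safety monitoring by the therapists stays as it is. The cost is one added form, a few extra minutes at assessments that already take place with staff already assigned, and more minor events recorded in both arms. One limit remains: a participant who leaves before the final assessment may still be represented by the log alone, and the report should say so.

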#### Primary outcome

The primary outcome of this study is the change in the MIP % predicted from baseline to the post-intervention timepoint (Week 2). MIP is a widely recognized and reliable indicator for assessing diaphragmatic function [37, 38]. Raw MIP scores were standardized according to the method of Evans and Whitelaw (males = 120 **−** (0.41** × **age); females = 108 **−** (0.61** × **age)) [39]. To account for established variations in MIP attributable to age and gender, the results are expressed as a percentage of predicted values.

#### Secondary outcomes

The secondary outcomes include changes in peak inspiratory flow (PIF), airway clearance ability, anxiety levels, quality of life, the decannulation rate, and the incidence of adverse events.

##### PIF

The PIF serves as a key parameter reflecting the velocity of diaphragmatic contraction. Higher PIF values indicate an increased capacity to overcome airway resistance [40].

##### Airway clearance ability

The Semi-Quantitative Cough Strength Score (SCSS) [41] is a 6-point ordinal scale (0–5) that has been validated for the assessment of cough efficacy as follows: 0: no cough; 1: visualized cough (oral airflow present) without sound; 2: barely audible cough; 3: distinctly audible cough; 4: forceful cough; and 5: sustained vigorous coughing. The SCSS will be assessed during brief manual occlusion of the tracheostomy stoma.

##### Anxiety levels

Anxiety will be measured using the standardized Zung Self-Rating Anxiety Scale (SAS), which is a widely applied instrument with established psychometric properties [42].

##### Quality of life

Quality of life will be evaluated using the Chinese version of the Tracheotomy-Specific Quality of Life (TQOL) scale [43]. This instrument, which was adapted through rigorous cross-cultural validation, comprises four domains—physical functioning, somatic status, social/family interaction, and overall satisfaction—and has been demonstrated to have high reliability and content validity.

##### Tracheotomy tube extraction rates

The decannulation rate will be recorded for both the intervention and control groups over the 2-week intervention period. Decannulation decisions will be made by clinicians who will be blinded to patient allocation, following the evidence-based protocol of the Chinese Expert Consensus on Tracheotomy Decannulation in Adults (2023) [44]. The specific protocol is presented in Fig. 3.

**Fig. 3 Fig3:**
[figure not shown]
Patient management pathway for tracheostomy decannulation

### Participant timeline {13}

The details of the timeline are presented in Table 1.

**Table 1 Tab1:**
[figure not shown]
Schedule of enrollment, intervention, and assessments

### Sample size calculation {14}

The sample size was determined based on the primary outcome (change in MIP% predicted). Using data from Bissett et al.’s RCT where high-intensity IMT demonstrated a mean improvement of 17% (SD = 4%) versus 6% (SD = 3%) in controls [24], we conservatively estimated a mean difference of 8% between groups. To account for greater clinical heterogeneity in tracheostomized patients, we adopted a pooled SD of 9% (versus 3.54% in Bissett’s study). Using G*Power 3.1 with a two-tailed *t*-test (*α* = 0.05, power = 0.90, allocation ratio 1:1), the initial calculation indicated 28 participants per group (total *N* = 56). Considering a 20% attrition rate (based on Bissett’s reported 17% loss to follow-up), the adjusted sample size was 35 per group (total *N* = 70).

### Recruitment {15}

A total of 70 tracheostomized patients will be recruited from the Sixth Affiliated Hospital of Sun Yat-sen University. A multidisciplinary collaborative network will be established to facilitate screening and referral of eligible candidates on the basis of the predefined inclusion criteria. Recruitment announcements will be posted on the hospital’s public website. Neutral informational materials describing IMT as an experimental respiratory training technique will be available in inpatient wards and outpatient clinics. A dedicated study coordinator will conduct individual consultations with eligible candidates to explain the study objectives, procedures, and safety considerations; address any concerns; and assist with the informed consent process.

## Assignment of interventions: allocation

### Sequence generation {16a}

The randomization sequence will be generated using SPSS version 26.0 by a researcher who is not involved in trial operations or outcome assessments. A simple randomization strategy will be employed to assign participants in a 1:1 ratio to either the HI-IMT group or the control group.

### Concealment mechanism {16b}

Allocation concealment will be ensured through the use of sealed, opaque envelopes. Each envelope will contain the group assignment and will be opened by the study investigator immediately before the initiation of the intervention.

### Implementation {16c}

The randomization sequence will be prepared by an independent statistician who will not be involved in participant recruitment or intervention delivery. Clinical staff will enroll eligible participants, and an independent researcher will assign interventions on the basis of the sealed envelope system.

## Assignment of interventions: blinding

### Who will be blinded {17a}

This is a single-blind trial. The participants will be blinded to group assignment. Owing to the nature of the intervention, it is not feasible to blind the therapists conducting the training. However, outcome assessors and the data analyst will remain blinded to the group allocation to minimize bias during outcome analysis.

### Procedure for unblinding if needed {17b}

Unblinding will be permitted only if a serious adverse event occurs that requires immediate clinical intervention or after the completion of final statistical analyses. Any unblinding must be approved by the principal investigator and documented in the case report form (CRF).

## Data collection and management

### Plans for assessment and collection of outcomes {18a}

Two trained research personnel will be present during each outcome assessment who will be blinded to the participants’ group allocation: one responsible for guiding the participant and the other for real-time data documentation. Both assessors must have prior experience and standardized training in outcome evaluation. Data will be recorded directly on the CRF and signed and dated by both staff members. Demographic data will be collected during the initial session. Details of the outcome measures are provided in the “Outcomes {12}” section.

### Plans to promote participant retention and complete follow-up {18b}

During the first session, the participants will be clearly informed about the importance of attending all the scheduled sessions through the end of the study. Only those who are able to fully comply with the protocol will be enrolled. The importance of adherence will be emphasized throughout the intervention period. Participants who discontinue the study will be recorded as dropouts.

### Data management {19}

All the participant data will be documented on individual CRFs and deidentified using unique study codes. Personal identifiers will not be recorded. All the data will be securely stored in locked file cabinets that are accessible only to authorized members of the research team. No data will be shared.

### Confidentiality {27}

Data confidentiality procedures are outlined in the “Plans for assessment and collection of outcomes {18a}” and “Data management {19}” sections.

### Plans for collection, laboratory evaluation, and storage of biological samples for genetic or molecular analysis in this trial/future use {33}

Not applicable, as this study will not involve the collection, storage, or analysis of biological samples.

## Statistical methods

### Statistical methods for primary and secondary outcomes {20a}

Statistical analyses will be conducted in accordance with the CONSORT guidelines to ensure methodological transparency and rigor [45]. The primary analytical approach will follow the intention-to-treat (ITT) principle, including all randomized participants irrespective of adherence to the intervention. In cases where the percentage of missing data exceeds 20%, multiple imputation will be applied using predictive mean matching for continuous variables. Sensitivity analyses will also be conducted, comparing ITT and per-protocol (PP) populations. The PP population will consist of participants who complete at least 80% of the scheduled training sessions, enabling evaluation of result robustness.

The data will be analyzed with SPSS version 26.0. The normality of continuous variables will be assessed using the Shapiro–Wilk test and visual inspection of histograms. Between-group differences in the MIP will be analyzed with independent samples *t* tests (for normally distributed data) or Mann–Whitney *U* tests (for nonnormally distributed data). The secondary outcomes will be analyzed as follows: continuous variables will be compared between groups with t tests or Mann–Whitney *U* tests on the basis of distributional assumptions. Ordinal outcomes will be evaluated with Wilcoxon rank-sum tests. Binary outcomes will be analyzed with chi-square tests or Fisher’s exact tests for small sample sizes. Adverse events will be summarized descriptively by frequency and severity.

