### Methods in analysis to handle protocol non‑adherence and any statistical methods to handle missing data {20c}

An ITT approach will be used for all primary and secondary outcome analyses. Multiple imputation will be employed to address missing data, ensuring statistical validity.

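### Items 20a and 20c give different rules for missing outcomes, and the plan's own attrition figures do not exceed the 20% trigger, so the all-randomised analysis is not secured

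*Protocol article*

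**What the plan says.** Item 20a (Statistical methods for primary and secondary outcomes) makes intention to treat the primary approach, "including all randomized participants irrespective of adherence to the intervention". It then makes imputation conditional: "In cases where the percentage of missing data exceeds 20%, multiple imputation will be applied using predictive mean matching for continuous variables". It does not say whether the percentage is counted over participants, within an arm, per variable or over all data cells, and it gives no method for missing outcomes at or below 20%. The primary comparison is an independent-samples t test or a Mann–Whitney U test. The stated sensitivity analysis compares the intention-to-treat set with a per-protocol set defined by completing at least 80% of sessions.

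Item 20c (handling of non-adherence and missing data) says "An ITT approach will be used for all primary and secondary outcome analyses" and continues: "Multiple imputation will be employed to address missing data, ensuring statistical validity". It attaches no condition.

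Item 14 (Sample size calculation) inflates 28 per group to 35 per group: "Considering a 20% attrition rate", with reference to a 17% loss in the trial used for planning.

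**The concern.** The two items give different answers whenever some, but not more than 20%, of the data are missing: item 20c imputes and item 20a does not. That is the range in which the plan's own attrition figures lie. Under item 20a the participants without a Week 2 value would then have no route into the primary test, although the analysis would still be described as including everyone randomised.

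Two things are at stake. First, the primary method would be settled only once the amount of missing data is known, and the undefined denominator leaves a further choice open at that time. Second, a percentage threshold says nothing about bias, which depends on why values are missing. The protocol contains a possible route to informative loss. Item 11b withdraws participants who repeatedly meet the discontinuation criteria, item 18b records those who discontinue as dropouts, and only the HI-IMT arm trains against a load (item 11a). Loss that differs by arm and is related to tolerance is therefore possible, although the protocol gives no figure for it.

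**Working it through.** **Inputs.** From item 14: difference 8 points, SD 9, two-sided alpha 0.05, power 0.90, 28 per group before and 35 per group after 20% attrition, and 17% loss in the cited trial. From item 20a: imputation only above 20%.

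**1. The plan's sample size.** The normal approximation is n = 2(1.960 + 1.282)² × 9² / 8² = 2 × 10.51 × 81/64 = 26.6, so 27 per group. With the noncentral t distribution, power is 0.893 at 27 and 0.904 at 28, so 28 per group is reproduced. Then 28 / (1 − 0.20) = 35 per group, total 70. The sample size itself is sound.

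**2. Planned loss against the trigger, counting participants.**
- Planned: 70 − 56 = 14, and 14/70 = 20.0%. This equals 20% and does not exceed it.
- Cited trial: 0.17 × 70 = 11.9, below the trigger.
- Exceeding 20% of 70 requires at least 15 missing.

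Without imputation, the test would use 70 − 14 = 56 participants at the planned rate, or about 70 − 12 = 58 at 17%.

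**3. Chance that the trigger is met.** Assume each participant drops out independently with probability p, so the number missing is Binomial(70, p).

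| True rate p | Expected missing | P(at least 15 missing) |
|---|---|---|
| 20% (planned) | 14.0 | 0.43 |
| 17% (cited) | 11.9 | 0.20 |
| 15% (assumed) | 10.5 | 0.09 |
| 10% (assumed) | 7.0 | 0.003 |

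Under item 20a, no imputation is the more likely course at both planning rates: 1 − 0.43 = 0.57 and 1 − 0.20 = 0.80.

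**4. The denominator matters.** If the percentage is counted within an arm, exceeding 20% of 35 means at least 8 missing. The chance that at least one arm reaches this is 0.64 at 20% and 0.41 at 17%. At a true 20%, the choice of denominator alone moves the chance of imputation from 0.43 to 0.64.

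**5. Assumed illustration of complete-case bias.** Suppose the 7 least tolerant of 35 HI-IMT participants (20% of the arm) and no controls are lost, and tolerance correlates with MIP gain at ρ. Dropping the lowest 20% of a normal variable raises the mean of the rest by φ(−0.842)/0.80 = 0.280/0.80 = 0.35 SD. The gain among completers therefore rises by 0.35 × ρ × 9.
- ρ = 0.3: 0.9 points, so the difference is 8.9 instead of 8.
- ρ = 0.5: 1.6 points, so 9.6.
- ρ = 0.7: 2.2 points, so 10.2.

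In simulation with no true effect, the nominal 5% test rejects in about 7%, 11% and 16% of trials. The correlations and the one-sided loss are assumptions, not figures from the protocol. The scenario loses 7 of 70, or 10% overall, so with participants as the denominator item 20a would not impute.

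**The case against.** The best defence is that item 20c states the general approach and item 20a adds when and how it applies. That reading is coherent, but item 20c carries no condition. Even on that reading nothing keeps participants with missing outcomes in the analysis at or below 20%, so the conflict with the all-randomised definition remains.

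Some stronger readings are tempting, and the documents do not support them:
- A reader might infer that the trigger can never be met. The planning figures do not exceed it, but observed missingness may well do so, as step 3 shows.
- A reader might take the complete-case analysis as stated. It is an inference: the protocol is silent at or below 20%, but the tests it names cannot use a participant whose outcome is neither observed nor imputed.
- A reader might take step 5 as the harm done by the trigger, or as the gain from deleting it. It shows only the bias of a complete-case comparison when loss depends on tolerance in one arm. Multiple imputation assuming data missing at random would remove that bias only as far as observed covariates capture tolerance.
- A reader might call differential loss likely. Under items 11a and 11b training is first paused and the load held, and withdrawal needs repeated events, so the protocol supports no more than possible.

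The imputation model for the ordinal cough score, the full covariate list and whether to impute within arm are details commonly left to an analysis plan. They are not faults here. It is also fair to note that the trial is short and described as exploratory.

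**Conclusion.** The point stands as a should-fix. Items 20a and 20c need to be reconciled, and item 20a as written does not deliver the all-randomised analysis that it declares. At the plan's own attrition figures (14 of 70, or about 12 of 70) its rule gives no imputation, which by inference leaves about 56 to 58 of 70 in the primary test. Whether imputation is triggered turns on a single participant (14 or 15 missing) and on an unstated denominator. The probabilities of 0.43 and 0.20 rest on independent dropout and on counting participants out of 70. How far the result would be biased cannot be known from the protocol; the figures in step 5 are illustrative only. The planned comparison with the per-protocol set does not settle the matter, because it examines adherence and leaves the missing-data assumption untested.

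**What to change.** Delete the 20% trigger and replace the two statements by one rule in items 20a and 20c: missing Week 2 outcomes are multiply imputed at any level of missingness, with predictive mean matching for continuous outcomes, so that all 70 randomised participants enter the primary analysis. The imputation can use data the protocol already collects, such as baseline MIP% predicted and the MIP re-measured at the start of the second week (controls follow the same evaluation protocol).

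Report two sensitivity analyses for the missing-data assumption: the complete-case analysis, and a delta-adjusted analysis that lets unobserved outcomes be worse than the imputation model predicts. The per-protocol comparison can stay as a supplementary check on adherence.

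The cost is a wording change and modest analysis work, with no new data and no change to the sample size. Recruitment began in August 2025, so the rule should be fixed and recorded as an amendment before outcome data are examined.

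### The primary test is chosen after the data are seen by a normality check, and its Mann–Whitney branch does not address the mean difference of 8 points on which the trial is sized

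*Protocol article*

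**What the plan says.** Statistical methods {20a} sets out a two-stage rule. First, "The normality of continuous variables will be assessed using the Shapiro–Wilk test and visual inspection of histograms". Then "Between-group differences in the MIP will be analyzed with independent samples" t tests if the data are judged normal, or Mann–Whitney tests if not. No cut-off for the Shapiro–Wilk test is given. It is not said whether the check is made per arm or on the pooled data, or which check prevails if the test and the histogram disagree. The Abstract repeats the open choice between parametric and non-parametric tests.

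Outcomes {12} defines the primary outcome as the change in MIP% predicted from baseline to week 2. Sample size calculation {14} is built on a mean: "we conservatively estimated a mean difference of 8% between groups", "we adopted a pooled SD of 9"%, and a "two-tailed *t*-test (*α* = 0.05, power = 0.90, allocation ratio 1:1").

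On missing data, {20a} brings in multiple imputation only when more than 20% is missing, whereas {20c} says without a threshold: "Multiple imputation will be employed to address missing data, ensuring statistical validity".

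**The concern.** The two branches ask different questions. The t test compares mean change, which is the quantity the trial was sized for. Mann–Whitney asks whether a patient in one arm tends to have a larger change than a patient in the other. It neither tests nor estimates the mean difference unless the two distributions differ only by a shift. Which question the primary analysis answers depends on a test result and on a visual judgement, both made on the trial's own outcome data. A significance verdict can turn on that choice, and on one branch the primary p-value does not belong to the effect of 8 points.

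Imputation adds a practical difficulty. A U statistic or its p-value is not an estimate with a standard error, so it does not enter standard pooling directly, and the normality verdict could differ from one imputed data set to the next.

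**Working it through.** **Step 1: reproduce the plan's figure.** Inputs from {14}: difference 8, SD 9, two-sided α 0.05, power 0.90, allocation 1:1.
- Standardised effect: d = 8/9 = 0.889.
- Power comes from the noncentral t distribution with 2n − 2 degrees of freedom and noncentrality d·√(n/2).
- n = 27: noncentrality 0.889 × √13.5 = 3.27, power 0.893.
- n = 28: noncentrality 0.889 × √14 = 3.33, power 0.904.

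So "the initial calculation indicated 28 participants per group" is right. "Considering a 20% attrition rate", 28/(1 − 0.20) = 35 per group, 70 in all. The sample size is correct for a t test on the mean.

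**Step 2: how often the check diverts the trial.** The article gives no cut-off, so assume Shapiro–Wilk p<0.05 in either arm. With truly normal data the expected rate is 1 − 0.95² = 9.75%. Simulation at 28 per arm gives about 10%. Under skew it gives about 66% for gamma with shape 4 and about 90% for lognormal with σ = 0.5. The histogram step cannot be simulated.

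**Step 3: error and power when both arms have the same shape.** 28 per arm, 5,000 runs under the null and 3,000 at d = 8/9:

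| Shape | Type I error, t | Type I error, two-stage | Power, t | Power, two-stage | t and Mann–Whitney disagree at d = 8/9 |
|---|---|---|---|---|---|
| Normal | 0.051 | 0.051 | 0.900 | 0.901 | 4.0% |
| t, 5 df | 0.049 | 0.047 | 0.908 | 0.941 | 5.5% |
| Lognormal, σ 0.5 | 0.046 | 0.049 | 0.902 | 0.967 | 7.1% |
| Exponential | 0.049 | 0.056 | 0.898 | 0.985 | 8.9% |

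Separate runs of 4,000 trials gave disagreement at d = 8/9 of 3.3–3.6% (normal), 4.5–4.8% (gamma, shape 4) and 6.7–8.0% (lognormal). At a smaller effect of 0.6 SD it was about 6–17% over the same three shapes.

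**Step 4: equal means, unequal spread.** The SDs that {14} quotes from the earlier trial are 4% and 3%, a ratio of 4/3. With equal means and that ratio, the two-stage rule rejects in 5.8% (gamma, shape 4), 7.2% (lognormal) and 10.4–10.9% (exponential) of trials. The t test rejects in 4.5–5.5%. With normal data the two-stage rule rejects in 5.4%. At a ratio of 2 with exponential data the figures are about 24% against under 6%. These excess rejections are not errors about rank ordering. They show that the Mann–Whitney branch is testing something other than the mean.

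**Step 5: pooling.** The probability that a patient in one arm exceeds a patient in the other, on the logit scale, was pooled by Rubin's rules over 20 imputations (35 per arm, 20% missing, exponential data). It rejected in 4.1% of null trials and 96% at d = 8/9. A Mann–Whitney effect measure can therefore be pooled, although U itself cannot be entered directly.

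**The case against.** The fork is written down in advance, with two named tests and a stated direction. {17a} blinds the data analyst, which limits steering towards a favoured arm, and {8} labels the trial exploratory. The two-stage rule holds about 5% type I error when the arms have the same shape, and it gains power under skew (0.96 against 0.89 for lognormal in one run). Raw disagreement between the tests also overstates the effect of the rule: with normal data at the planned effect, the two-stage verdict differs from the t test in only 0.4% of trials. The excess rejections in step 4 need skew together with unequal spread, and nothing in the article shows that MIP data will look like that.

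Most of this stands and limits the point. Blinding and the exploratory label reduce the discretion but do not fix the test or the quantity in advance.

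A reader might go further in four ways that the document does not support:
- **That the Mann–Whitney branch cannot be pooled.** Step 5 shows that it can, through an effect measure. A pooling rule is the kind of detail an analysis plan may hold. Under {20a}, attrition of exactly the planned 20% would not even trigger imputation.
- **That the normality check inflates type I error in general.** Step 3 shows otherwise.
- **That the sample size is wrong.** Step 1 reproduces it.
- **That no mean difference would be reported if Mann–Whitney supplied the p-value.** {20a} names tests and does not say this.

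**Conclusion.** The point holds in a limited form. The protocol itself, not a missing analysis plan, makes the primary test depend on the data and partly on a visual reading, and one of the two branches does not match the powered quantity. The size is moderate: the two tests differ on p<0.05 in about 4–8% of trials at the planned effect, and the two-stage rule rejects in about 6–11% of trials with no mean difference if data are skewed with an SD ratio of 4/3, against about 5% for the t test. The t test alone held about 5% in every shape tried, so the check is not needed to protect error. These figures rest on assumed distributions and an assumed trigger of p<0.05 in either arm; checking pooled residuals once would divert about 5% of normal trials instead of 10%. The harm is an open choice of test and an unsettled target quantity.

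**What to change.** In {20a}, remove the normality check for the primary outcome and name one analysis: a linear model of week-2 (or change in) MIP% predicted, adjusted for baseline MIP% predicted. Report the adjusted mean difference with its 95% confidence interval, pooled by Rubin's rules if imputation is used. Robust standard errors are optional. Keep Mann–Whitney as a labelled sensitivity analysis. Fixing a plain or Welch t test on the change score would also close the fork; the baseline adjustment is preferred because the baseline value is already collected. The Abstract, which speaks of unadjusted comparisons by either type of test, should then be brought into line.

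The cost is wording, plus some power if the data are heavily skewed: about 0.89 for the unadjusted t test against 0.96 for the two-stage rule with lognormal data at the planned effect. The sample size stays at 35 per group.
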